### Methods in analysis to handle protocol non-adherence and any statistical methods to handle missing data {20c}

A modified “as-randomized” analysis (or “intention-to-treat” analysis) will be used. One pre-specified modification to the analytic set is the exclusion of randomized infants who are not subsequently extubated for new/emergent conditions not known at time of randomization. This number is expected to be minimal and will be closely monitored. All other infants will be included in the analysis under standard ITT assumptions.

### Plans to give access to the full protocol, participant-level data, and statistical code {31c}

We will use CONSORT guidance for reporting results [32]. De-identified participant-level data and code in support of each publication will be made available within 6 months of publication. Limited risk data files will be available at the end of the study under a data use agreement.

## Oversight and monitoring

### Composition of the coordinating center and trial steering committee {5d}

#### The executive committee

The DIVA executive committee consists of the clinical coordinating center (CCC) PIs and DCC PI. This committee assumes ultimate responsibility for the following:Ensure study policies and procedures are implemented at study sitesDetermine whether concurrent enrollment in other studies at the sites is acceptableDraft protocol amendments when neededLiaise at arm’s length with the DSMB and review and act upon DSMB recommendationsEnsure the rate of enrollment is satisfactory and that this is adhering to the study milestonesLiaise with the technical committee and steering committeeEnsure new pertinent literature is disseminated to the steering committee and DSMBApprove the final manual of procedures and case report forms (CRFs)Monitor trial performance across sitesEnsure that serious adverse events and adverse events are reported promptly according to IRB and DSMB timelinesIdentify poorly functioning sites and implement remedial procedures and, if needed, remove the site from the trialAdd new sites if needed to meet enrollment milestones

#### The clinical coordinating center (CCC)

The CCC will direct the clinical aspects of protocol development and study implementation and will be the primary liaison with the site IRBs.

#### The data coordinating center (DCC)

The DCC has statistical operations centered at the UVA and data management operations at the University of Pennsylvania, Philadelphia PA. The DCC will provide statistical collaboration, data management, and information technology support for the development and conduct of the trial. The DCC is responsible for regulatory oversight and coordination of protocol modifications at the participating clinical sites.

#### The technical committee

The DIVA technical committee comprises experts in neonatal respiratory management and, in particular, NAVA. The technical committee will be responsible for developing training materials, training study teams in NIV-NAVA and NS-NIPPV, monitoring study interventions, and providing guidance and troubleshooting questions that arise in ventilator management for all study sites.

#### The steering committee

In addition to the executive and technical committee members, the steering committee will consist of each site PI, two expert advisors with extensive expertise leading neonatal trials of respiratory management, and an NHLBI scientist.

### Composition of the data monitoring committee, its role and reporting structure {21a}

All US sites will use a single IRB (sIRB, University of Pennsylvania), and all reportable events will be submitted to this IRB for initial assessment adhering to the National Institutes of Health (NIH) sIRB policy. International sites will use individual review boards rather than a single IRB. A data safety monitoring board (DSMB) was appointed by the NHLBI (see details below).

The data safety monitoring board (DSMB) is an independent group tasked to provide recommendations to the Office of the Director, NHLBI, including recommendations about starting, continuing, and stopping the study. The DSMB will receive regular reports from the trial on any injuries or adverse events, any developments that jeopardize the continued success of the trial, and data by which to accomplish the evaluation of pre-determined early stopping rules [33].

### Adverse event reporting and harms {22}

Adverse events will be monitored during the study intervention and follow-up phases to ensure timely detection of events that may affect safety or continued participation. Reportable events will be reported to the DCC, who will then ensure all events are reported to the IRB and DSMB.

Pre-specified reportable trial SAEs include:New air leaks (pneumothorax or pulmonary interstitial emphysema)New gastrointestinal perforation or bleeding (theoretical concern from Edi catheter)Death

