### Respiratory management

Protocol-mandated aspects of respiratory management during the intervention period include the following:Infants will be managed according to their allocated support mode for 5 days (120 h) after extubation, with no cross-over between groupsNIV-NAVA will be delivered using the Servo-I, Servo-N, or Servo-U with the associated Edi catheter. All of these have FDA clearance for neonates weighing > 500 gInfants in the control arm will be managed using an FDA-approved respiratory device, per the study unit’s standard of careFor both treatment groups, respiratory support will be provided using an interface with FDA approval or clearance to provide continuous positive pressure for preterm infants. RAM cannula and other non-approved interfaces, therefore, will not be usedAll infants must be treated with systemic (enteral or parenteral) caffeine throughout the study intervention periodVentilator settings will be titrated according to local unit norms within the allowable DIVA protocol settings (Table 2). These reflect variations in site practice across all DIVA trial sites. Sites do not need to escalate parameters to the maximal values provided. Guidelines for escalating and weaning ventilator support in both arms are provided in the manual of operations

**Table 2 Tab2:** Range of allowable NIV-NAVA and NS-NIPPV settings

	**Intervention arm: NIV-NAVA**	**Control arm: NS-NIPPV**
PEEP	5–10 cm H_2_O	5–10 cm H_2_O
PIP	N/A, backup PIP 15–30 cm H_2_O	15–30 cm H_2_O
Rate	N/A, backup rate 10–60	10–60

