### Provisions for post-trial care {30}

Enrolled infants will be managed as directed by the local clinicians following the 5-day intervention period. Secondary and safety outcomes will be ascertained until 36 weeks’ PMA, death, or discharge (whichever comes first).

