## Data collection and management

### Plans for assessment and collection of outcomes {18a}

#### Study measures

Study measures will be ascertained from the maternal and infant medical records or collected from ventilator logs. Key data to be collected for all subjects allocated to treatment are listed in Table 5.

**Table 5 Tab5:** Key data to be collected for enrolled subjects

Topic and timing	Specific data elements
Pre-randomization characteristics	*Demographics*: birth weight, gestational age at birth, sex, race, ethnicity, multiple gestations, small for gestational age at birth, postnatal age at randomization *Maternal characteristics*: antenatal steroids, clinical diagnosis of chorioamnionitis, diagnosis of PPROM, mode of delivery *Postnatal interventions*: surfactant (number, timing, and method of administration), postnatal steroids *Respiratory interventions*: duration of mechanical ventilation, mode of ventilation and highest settings, ventilator settings at the time of extubation, postnatal age (days) at extubation, interval (hours) between extubation and initiation of allocated ventilator mode
Daily respiratory status, obtained daily for the first 5 days after treatment allocation	*Extubation failure criteria*: blood gas values, highest FiO_2_, number of apnea/bradycardia events over the previous 24 h Intubation, including timing and indication All respiratory settings and FiO_2_ values
Respiratory Status obtained weekly from treatment allocation until 36 weeks PMA	Timing and indication for all intubations Timing of extubation Start/stop dates of modes of support (i.e., invasive ventilation, non-invasive ventilation, CPAP, cannula, room air) Respiratory medications, including diuretics and postnatal steroids PMA at last invasive ventilation, positive pressure, and supplemental oxygen
Respiratory status at 36 weeks PMA	Respiratory support mode and settings at 36 weeks PMA Supplemental oxygen at 36 weeks PMA
Safety outcomes by 36 weeks PMA	Air leaks, GI perforation and bleeding, and death (date and primary cause of death; narrative autopsy results if performed)
Secondary clinical outcomes by 36 weeks PMA	Brain injury, retinopathy of prematurity, sepsis, patent ductus arteriosus, pulmonary hemorrhage, necrotizing enterocolitis Any surgical procedures

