## Statistical methods

### Statistical methods for primary and secondary outcomes {20a}

The proposed study is a two-arm parallel design of two alternative courses of treatment. A modified “as-randomized” analysis (or “intention-to-treat” analysis) (mITT) will estimate whether NIV-NAVA is superior to NS-NIPPV in avoiding treatment failure and is at least as good as NS-NIPPV in avoiding adverse events.

Among infants randomized before extubation, there is a risk that infants will become ineligible for extubation (and from the trial) after randomization due to changes in clinical status. Therefore, a mITT analysis has been planned. Only infants whose eligibility changes due to new/emergent conditions not known at the time of randomization will be excluded from the primary outcome analysis set in the mITT analysis. This number is expected to be minimal and will be closely monitored. A sensitivity analysis using a conventional ITT analysis will also be conducted.

The primary outcome will compare rates of extubation failure between the treatments using logistic regression. The regression model will be fitted using robust clustered standard errors under the generalized estimating equation (GEE) framework, with an exchangeable correlation structure for clusters based on infant mother, i.e., adjusting for the inherent correlation between infants that are multiples. The primary analysis will include clinical site, gestational age, biological sex, and days of invasive ventilation prior to extubation as fixed effects, to control for any residual confounding and site-level treatment imbalance from the stratification factors. Standard regression diagnostics will be used to assess model adequacy and to examine for potential outlying or influential data points.

Secondary efficacy and safety outcomes will be analyzed using similar procedures to the primary outcome. Comparisons between treatment arms will use GEE based logistic regression (dichotomous outcomes), linear regression (continuous outcomes), Poisson regression (count outcomes), or survival analysis (time based outcomes), as appropriate.

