## Discussion

### Synchronizing non-invasive ventilation: testing a novel method

Non-invasive positive pressure support is used to stabilize alveolar recruitment and provide chest wall stability to prevent the need for invasive ventilation and decrease rates of BPD, as demonstrated in observational trials, randomized controlled trials, and meta-analyses [26, 34–39]. Available modes of non-invasive support have included CPAP and NIPPV. CPAP failure is common, and a Cochrane review and meta-analysis have demonstrated that both synchronized and non-synchronized NIPPV are superior to CPAP at preventing extubation failure, but only synchronized NIPPV reduced the incidence of BPD when compared to CPAP [40, 41].

Synchronizing NIPPV in preterm infants is challenging because of the large interface leaks, high respiratory rates, small tidal volumes, and variable breathing patterns inherent to this population. A Graseby pneumatic capsule, which is a small foam-filled disc secured to the abdominal wall to detect tiny pressure changes, has been used but has limitations due to difficulties with capsule positioning and attachment, inaccuracy at fast respiratory rates, motion artifact, and sensitivity-detecting respirations [42–44]. Another option, non-invasive flow triggering, is often inaccurate due to large and fluctuating leaks [45, 46].

NIV-NAVA provides an innovative method to synchronize non-invasive respiratory support with infant respiratory drive. NAVA detects the diaphragm’s electrical activity of the diaphragm (Edi) using a functional naso/orogastric tube with imbedded electrodes and delivers assistance that is synchronized and proportional to the infant’s respiratory drive [47, 48]. Because the neural signal is detected by the Edi catheter in the esophagus, it functions independently of air leaks and motion artifacts, has a rapid response rate, and is therefore synchronous in both invasive and non-invasive ventilation [49].

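### The gastrointestinal safety item tied to the Edi catheter counts events at any site to 36 weeks PMA, so on its own it cannot separate upper-GI catheter injury from bowel events

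*Protocol article*

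**What the plan says.** The item, "gastrointestinal perforation or bleeding", appears three times in the protocol article. It is in the list under Secondary study endpoints. It is in Table 5 (Study measures) among the safety outcomes as "Air leaks, GI perforation and bleeding, and death". Under Adverse event reporting and harms {22} it reads "New gastrointestinal perforation or bleeding (theoretical concern from Edi catheter", which is the only reason given for it. None of the three names an anatomical site.

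The article does say where the device sits. The Discussion states "Because the neural signal is detected by the Edi catheter in the esophagus", and the eligibility criteria treat it as a naso/orogastric catheter and exclude infants with esophageal bleeding.

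Two time frames apply. On exposure, Respiratory management says "Infants will be managed according to their allocated support mode for 5 days (120 h) after extubation". On follow-up, Provisions for post-trial care {30} says "Secondary and safety outcomes will be ascertained until 36 weeks", here meaning PMA, with death or discharge ending it earlier.

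Table 5 lists "necrotizing enterocolitis" separately among the secondary clinical outcomes, but nothing removes its perforations or bleeds from the GI item. The Statistical methods section {20a} sets the safety aim that NIV-NAVA "is at least as good as NS-NIPPV in avoiding adverse events" and analyses safety outcomes by procedures similar to those for the primary outcome.

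**The concern.** The suspected harm belongs to one region, the esophagus and stomach, while the item covers the whole gastrointestinal tract. It also runs for weeks beyond the period in which the arms must differ. A bowel perforation in either arm counts the same as an esophageal injury in the NIV-NAVA arm.

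In an efficacy comparison such dilution is conservative. Here the aim is to show that NIV-NAVA is no worse, so unrelated events common to both arms push the result towards the conclusion that the trial hopes to draw. If a catheter injury exists, the reported odds ratio for the pooled item would be pulled towards 1, and a reader could take a non-significant result as reassurance about the catheter.

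**Working it through.** **Sample size basis.** Sample size {14} gives 406 infants, a design effect of 1.15 and 2% drop-out. Rounding up per arm: 203 × 1.15 = 233.5, so 234; 234 / 0.98 = 238.8, so 239; 2 × 239 = 478. This reproduces the stated total, which concerns extubation failure and is not in dispute. Evaluable infants per arm: 478 × 0.98 / 2 = 234.

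**Assumptions.** The article gives no GI event rate. I take a background of 0.5% or 1% for esophageal or gastric events, and 1%, 5%, 8% or 12% for all sites pooled. The catheter adds the same absolute excess *e* to either endpoint in the NIV-NAVA arm.

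**How the dilution works (e = 3 points).** The expected excess is 234 × 0.03 = 7.0 events on either endpoint. The standard deviation of the difference in counts is √{n[p₀(1−p₀) + p₁(1−p₁)]}:

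- Upper GI, 0.5% v 3.5%: √[234 × (0.0050 + 0.0338)] = 3.0; ratio 7.0 / 3.0 = 2.3.
- Pooled, 5% v 8%: √[234 × (0.0475 + 0.0736)] = 5.3; ratio 1.3.
- Pooled, 12% v 15%: √[234 × (0.1056 + 0.1275)] = 7.4; ratio 0.95.

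The planned logistic model would estimate odds ratios of:

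- Upper GI: (0.035/0.965) / (0.005/0.995) = 7.2.
- Pooled at 5%: (0.08/0.92) / (0.05/0.95) = 1.65.
- Pooled at 12%: (0.15/0.85) / (0.12/0.88) = 1.29.

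**Power.** For each pair of rates, I summed the binomial probabilities of all pairs of counts that reject at two-sided 5% with the excess in the NIV-NAVA arm. There are 234 infants per arm and no clustering.

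| Endpoint, background | e = 3 points: Fisher / z | e = 2 points: Fisher / z | e = 1 point: Fisher / z |
|---|---|---|---|
| Upper GI, 0.5% | 54% / 68% | 27% / 43% | 5% / 17% |
| Upper GI or pooled, 1% | 44% / 57% | 22% / 33% | 6% / 13% |
| Pooled, 5% | 21% / 26% | 11% / 14% | 5% / 7% |
| Pooled, 8% | 16% / 20% | 9% / 11% | 4% / 6% |
| Pooled, 12% | 12% / 16% | 7% / 9% | 4% / 5% |

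The z test is liberal with counts this sparse and Fisher's test is conservative, so the two bracket a reasonable answer.

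**Clustering.** If the plan's design effect of 1.15 also applied here, the effective size would be 234 / 1.15 = 203 per arm. Fisher power for a 3-point excess would then be 45% (upper GI, 0.5%), about 17% (pooled, 5%) and 11% (pooled, 12%). The ordering does not change.

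**The case against.** The strongest reply is that an article's outcome list is not an operational definition. The article refers to a manual of procedures and case report forms that are not shown, and these may record site, timing and cause. Nor does it say that all GI events will form one binary variable and that nothing else will be shown. This stands as a limit: the point concerns the item as worded. If the forms already capture site, only a reporting split is needed.

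Second, other routes to a signal exist. Each new event is reported to the data coordinating center and passed to the IRB and the DSMB, and necrotizing enterocolitis and surgical procedures are recorded separately. A rare device injury may be recognised from a single report without any test. This also stands, although it does not change what the pooled between-arm comparison can show.

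Third, the rates are assumed and the split endpoint is itself only modestly powered. That is correct. At a pooled background of 1%, Fisher power for a 3-point excess falls only from 54% (upper GI at 0.5%) to 44%. For a 1-point excess it is at most 6%, and at most 17% by the z test, on any definition.

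A reader might go further and infer that catheter harm is bound to be swamped and reported as no difference. The documents do not support that. They give neither a background rate nor a catheter-injury rate, and the DSMB sees individual events. Nor are all events after day 5 unrelated to the catheter, because local clinicians choose the support after that and NIV-NAVA may continue.

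Finally, all-site GI harm is a legitimate measure of overall safety. It should be kept, but it does not answer the catheter question.

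**Conclusion.** The point holds in a conditional form. The item is justified by a catheter in the upper tract but, as worded, covers every GI site up to 36 weeks PMA. On its own it therefore cannot distinguish catheter injury from bowel events, and a comparison of arms on it could miss a catheter effect.

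The direction does not depend on the test: for a fixed absolute excess of 2 or 3 points, power falls steadily as unrelated background rises, under both Fisher and z. The size does depend on assumed rates. With a 3-point excess and 0.5% upper-GI background, pooling at a 5% background cuts power by more than half. If pooled events are nearly as rare as upper-GI events, little is lost. This is a low-cost improvement to a safety definition. It is not an error in the sample size or in the primary analysis.

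**What to change.** Keep the pooled item for SAE reporting and as an overall safety measure. In the between-arm comparison also report:

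- (a) esophageal or gastric perforation or bleeding, as the catheter-harm endpoint, with perforation and bleeding tabulated separately;
- (b) intestinal perforation or bleeding, with or without necrotizing enterocolitis;
- (c) bleeding of undetermined site, as its own category.

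Classify by anatomical site and not by judged cause, because clinical staff know the allocation. Tabulate events in the 5-day intervention period separately from later ones, without treating the later ones as unrelated. Give each category with an estimate and confidence interval, and do not read a non-significant difference as evidence of no catheter harm.

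The cost is at most one site-of-event field on the form, if it is not already there, and a few table rows. The downside is fewer events and wider intervals in each category. Treatment and follow-up of infants do not change.

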### Frequency and plans for auditing trial conduct {23}

The executive committee will review sites’ screening logs, protocol violations, and deviations monthly. In the run-in phase, the technical committee will use an assessment tool to review NAVA performance and provide targeted feedback. In addition, the technical committee will audit ventilation management for the first six participants from each site during the randomization phase, regardless of treatment arm. Thereafter, the DCC will assign random technical audits of 10% of infants randomized to both arms throughout the randomization phase.

### Plans for communicating important protocol amendments to relevant parties (e.g., trial participants, ethical committees) {25}

Important protocol modifications (changes to eligibility criteria, outcomes, and analyses) will be promptly communicated to relevant parties. The sponsor and funder have been and will be notified of ethical approval and the clinical register record have been and will be updated.

### Dissemination plans {31a}

At the end of the trial, results will be submitted to the annual Pediatric Academic Societies (PAS) meeting, a high-profile general medical journal, and to ClinicalTrials.gov.

## Discussion

### Synchronizing non-invasive ventilation: testing a novel method

Non-invasive positive pressure support is used to stabilize alveolar recruitment and provide chest wall stability to prevent the need for invasive ventilation and decrease rates of BPD, as demonstrated in observational trials, randomized controlled trials, and meta-analyses [26, 34–39]. Available modes of non-invasive support have included CPAP and NIPPV. CPAP failure is common, and a Cochrane review and meta-analysis have demonstrated that both synchronized and non-synchronized NIPPV are superior to CPAP at preventing extubation failure, but only synchronized NIPPV reduced the incidence of BPD when compared to CPAP [40, 41].

Synchronizing NIPPV in preterm infants is challenging because of the large interface leaks, high respiratory rates, small tidal volumes, and variable breathing patterns inherent to this population. A Graseby pneumatic capsule, which is a small foam-filled disc secured to the abdominal wall to detect tiny pressure changes, has been used but has limitations due to difficulties with capsule positioning and attachment, inaccuracy at fast respiratory rates, motion artifact, and sensitivity-detecting respirations [42–44]. Another option, non-invasive flow triggering, is often inaccurate due to large and fluctuating leaks [45, 46].

NIV-NAVA provides an innovative method to synchronize non-invasive respiratory support with infant respiratory drive. NAVA detects the diaphragm’s electrical activity of the diaphragm (Edi) using a functional naso/orogastric tube with imbedded electrodes and delivers assistance that is synchronized and proportional to the infant’s respiratory drive [47, 48]. Because the neural signal is detected by the Edi catheter in the esophagus, it functions independently of air leaks and motion artifacts, has a rapid response rate, and is therefore synchronous in both invasive and non-invasive ventilation [49].

The neural trigger responds to the infant’s respiratory *drive*, in contrast to flow and pneumatic triggers which respond to the infant’s respiratory *effort*. The neural trigger is synchronous for initiation, size, and termination of the breath but flow and pneumatic triggers are synchronous for breath initiation only. Numerous small studies have demonstrated improved synchrony, lower peak pressures, and improved measures of oxygenation with the use of NAVA in infants [49–65]. However, no adequately powered studies have assessed the impact of NIV-NAVA on clinically relevant outcomes in preterm infants. The DIVA trial will fill this evidence gap.

